### 2.4. Sample Size Estimate

It was estimated that for this proof-of-concept study, it will be necessary to recruit 50 volunteer pregnant women. This sample size was determined considering that both parametric and non-parametric statistics will be performed.

According to Noether [23], when assuming a non-normal distribution, non-parametric statistical analyses require a sample size of 24 pregnant women, considering the Bonferroni correction (α = 0.025), desired statistical power, and appropriate effect size for non-parametric tests such as the Kruskal–Wallis test and Wilcoxon post hoc test [24].

If parametric statistical analyses are also planned (assuming a normal distribution), a sample size of 41 pregnant women is required, accounting for the Bonferroni correction (α = 0.025), with a statistical power of 0.80 and a significance level of 0.025. Considering a potential dropout rate of 20%, it is estimated that a total of 50 pregnant women should be recruited for the study.

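### Fifty recruits less 20% dropout leave 40 evaluable women, one short of the stated 41; the separate non-parametric figure of 24 cannot be checked as written

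*Protocol article*

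**What the plan says.** Section 2.4 of the protocol article gives two requirements and one total.

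- **Non-parametric.** "non-parametric statistical analyses require a sample size of 24 pregnant women". This is set "when assuming a non-normal distribution", at a Bonferroni-corrected alpha of 0.025. The other inputs are given only as "desired statistical power, and appropriate effect size for non-parametric tests such as the Kruskal–Wallis test and Wilcoxon post hoc test".
- **Parametric.** "If parametric statistical analyses are also planned (assuming a normal distribution), a sample size of 41 pregnant women is required", "with a statistical power of 0.80 and a significance level of 0.025". No effect size is given, and the test is not said to be one- or two-sided.
- **Total.** "Considering a potential dropout rate of 20%, it is estimated that a total of 50 pregnant women should be recruited for the study".

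Section 2.8.1 plans comparisons of baseline with post-intervention values within the same sample (paired t-test, Wilcoxon, sign test). The Limitations section confirms that there is no control group.

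**The concern.** Three figures in one short section (41 needed, 20% dropout, 50 recruited) should agree with each other, and they do not. If dropout is as assumed, the study ends with fewer women than its own calculation requires, so the stated 80% power is slightly too high.

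The second issue is how a reader takes the 24 when it stands beside 41 at the same alpha. It suggests that if the scores turn out non-normal, the rank-based analysis needs far fewer women and has room to spare at about 40 completers. Whether that is so depends on inputs that the section does not give.

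**Working it through.** **Inputs from section 2.4:** 41 evaluable women (parametric), 24 (non-parametric), alpha 0.025, power 0.80 (stated for the parametric figure only), dropout 20%, total 50.

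**Assumptions, not in the document:** two-sided testing; standardised paired effect d = 0.5 (back-calculated below); normally distributed differences where stated.

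**1. The total of 50**

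- Multiplying up: 41 × 1.20 = 49.2, rounded up to 50. This matches the stated total, but the article does not show its formula, so the route is inferred.
- Dividing by the retained fraction: 41/(1 − 0.20) = 51.25, so 52.
- Completers from 50 recruits: 50 × 0.80 = 40, against 41 required.
- Dropout at which 50 recruits still leave 41: 1 − 41/50 = 0.18.

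**2. The 41 and the cost of losing one woman**

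Paired t-test power from the noncentral t distribution, with df = n − 1, noncentrality d√n and two-sided alpha 0.025:

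| n | d | Power |
|---|---|---|
| 41 | 0.5 | 80.5% |
| 40 | 0.5 | 79.3% |

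The smallest n that reaches 80% at d = 0.5 is 41, so d = 0.5 reproduces the plan's figure. A one-sided test would imply d of about 0.45. If the effect is instead tuned so that 41 gives exactly 80.0%, power at 40 is 78.9%. On any of these readings the loss is about one percentage point.

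**3. The 24, under the effect implied by 41**

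Noether's signed-rank formula is n = (z₁₋α/₂ + z₁₋β)² / (3(p′ − 0.5)²), with p′ = Φ(d√2) for normal differences.

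- z values: 2.241 + 0.842 = 3.083; squared, 9.505.
- d = 0.5: p′ = Φ(0.707) = 0.760, so n = 9.505/(3 × 0.260²) = 46.8, i.e. 47.
- Through the asymptotic relative efficiency of 3/π = 0.955: 41/0.955 = 42.9, i.e. 43.
- Working back from n = 24: p′ = 0.5 + 3.083/√72 = 0.863, so d = Φ⁻¹(0.863)/√2 = 0.77.

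Simulated signed-rank power with normal differences, d = 0.5 and two-sided alpha 0.025 is about 77–78% at n = 40.

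**4. Does non-normality account for 24?**

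Matching 24 to 41 needs a relative efficiency of 41/24 = 1.71. Simulated signed-rank power at n = 24 and d about 0.5 was:

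| Shape of differences | Power at n = 24 |
|---|---|
| Normal | 48–51% |
| Laplace | 63–65% |
| t, 3 df | 77–79% |
| Exponential, by direction of skew | 39% or 68% |

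The ranges cover separate runs. Only the very heavy-tailed case comes near 80%.

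**The case against.** **The dropout slip is immaterial.** It amounts to one completer or two recruits, and about one point of power. The 20% is itself only a planning guess, and the pre–post comparison is a secondary objective in a study whose Limitations section says that it does not aim to evaluate effectiveness. This stands as to size: no decision changes. It does not make the three figures agree.

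**The 24 does not contradict the 41.** A reader might infer that the two are incompatible. The document does not support that. It gives no effect size for either figure and no numerical power for the 24, and it assumes a different distribution for the 24. Two figures with different unstated inputs are unverifiable, not contradictory. This stands.

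**The rank test is not weaker in general.** A reader might also infer that the non-parametric fallback is always the less powerful route. That holds for near-normal differences. In the simulations with Laplace and t (3 df) differences, the signed-rank test had more power than the t-test on the same data. This stands too.

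**The 24 drives nothing.** The total of 50 rests on the larger figure, 41, and no analysis of 24 women is planned. This is correct, so only the impression that the 24 leaves is at issue.

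**The inputs may sit in the full protocol.** An article condenses, and missing inputs alone would not be a finding. The mismatch of tests is on the page, however: the 24 is tied to Kruskal–Wallis with Wilcoxon post hoc, a comparison of several groups, while section 2.8.1 plans paired tests in a single sample and does not name Kruskal–Wallis.

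**Conclusion.** The dropout point holds as a minor arithmetic error that needs no outside input: 50 recruits at 20% dropout leave 40 women, one below the stated 41, and 52 would be needed to retain 41. The consequence is about 79% power instead of 80%, assuming a paired t-test, two-sided alpha 0.025 and d = 0.5.

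The point about the 24 holds only conditionally. With the same effect, 80% power and near-normal differences, a signed-rank test needs about 43 to 47 women, and 24 would suffice only for d of about 0.77. As the section stands, the 24 cannot be verified and is not shown to be the requirement for the planned paired analysis. It should not be read as evidence that the rank-test fallback has ample margin: at 40 completers with d = 0.5 and normal differences, that fallback has about 77–78% power.

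**What to change.** Reword section 2.4, leaving recruitment at 50.

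1. Choose one restatement: either 50 recruits retain 41 evaluable women up to 18% dropout, or at 20% dropout 40 evaluable women give about 79% power (paired t-test, two-sided alpha 0.025, d = 0.5).
2. State the effect size and the sidedness behind the 41, with d = 0.5 confirmed or corrected by the study team.
3. For the 24, either give its effect size, power, distribution and test, matched to the paired comparison in section 2.8.1, or remove it. If a statement on the rank test is wanted, report its power at 40 completers (about 77–78% under the assumptions above).

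Replacing 24 with a requirement of 43 to 47 would not be mere rewording. It would become the section's larger requirement and, at 20% dropout, imply 43/0.80 = 53.75 to 47/0.80 = 58.75, i.e. 54 to 59 recruits. Reporting the power at 40 avoids this.

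The cost is a few sentences and a stated power about one point lower.

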### 2.5. Technological Tools

The technological component of the study is based on the TreC platform, which enables citizens of the Trentino province to access, manage, and share health and well-being information [25]. TreC stands for ‘Cartella Clinica del Cittadino’ and is a reliable, well-tested platform designed to be a ‘system of systems’ rather than a simple data hub. A central pillar of the TreC platform is the citizen/patient’s role in managing their own health-related data. TreC’s flexible architecture enables the collection and management of heterogeneous data, as well as the development and use of additional subsystems that provide specific functions.

The digital intervention designed in this research project, in particular, is available in the TreC mobile application called ‘TreC Mamma’. It can be downloaded via a link only sent directly to participants. The user authentication process takes place via the digital identity service (Public Digital Identity System-SPID or Electronic Identity Card-CIE).

### 2.6. Procedures

#### 2.6.1. Enrollment

Women who meet the inclusion criteria and provide informed consent will be enrolled in the study. Participation requires signing an informed consent form at the time of enrollment, following a thorough explanation of the study objectives, data collection and management procedures, the expected level of involvement, the study duration, and issues related to confidentiality. Participants will also be informed that they may withdraw from the study at any time, without the need to provide a reason and without any impact on the quality of care received or on the continuation of their medical treatment.

In addition, participants will receive detailed information regarding the processing of their personal data during the study. Copies of both the informed consent form and the privacy policy will be provided to each participant and will remain accessible within the application throughout the study period.

#### 2.6.2. Data Collection

Socio-demographic data will be collected using a pre-structured form at the time of enrollment by the midwives and doctors involved. Each participant will be given a unique alphanumeric code. This socio-demographic data sheet will be kept separately from the data collected during the study. The required socio-demographic data will be: (a) date of birth, (b) expected date of delivery, (c) level of education, (d) occupation, (e) marital status, (f) number of previous pregnancies and deliveries, (g) partner’s occupation, if applicable, (h) pre-pregnancy weight, and (i) height.

Women will also be asked if they would like to participate in focus groups and qualitative interviews one month after the intervention ends (Table 1). If they consent, they will be asked for a contact telephone number.

The psychoeducational path offered by Demetra begins and ends with the completion of self-report questionnaires, which takes approximately 15 min.

Specifically, six questionnaires will be administered at the beginning and end of the psychoeducational intervention to investigate depressive and anxiety symptoms, general well-being, experiential avoidance, psychological flexibility, and adherence to the Mediterranean diet. None of the questionnaires had a diagnostic purpose, so they will not be used to diagnose psychopathology, but only for the collection of descriptive data.

A further four questionnaires will be sent out during the course with the aim of analyzing usability and the woman’s involvement with the app and the virtual coach, Demetra. Specifically, the usability questionnaires will be administered at the end of the third (three questionnaires) and sixth (end of the study; four questionnaires) weeks.

The choice of the ten assessment instruments was guided by the need to evaluate the feasibility, acceptability, and theoretical consistency of the Demetra intervention with the principles of Acceptance and Commitment Therapy (ACT). The selected tools cover three complementary domains:Psychological variables—to detect changes in depressive and anxiety symptoms, overall psychological well-being, and psychological flexibility, which are directly relevant to ACT’s aim of increasing adaptive responses to internal experiences.Behavioral and lifestyle outcomes—to measure adherence to healthy dietary patterns and physical activity levels, which are explicit behavioral targets of the intervention.User experience and usability—to assess engagement, perceived quality, and usability of the app and virtual coach, which is crucial for evaluating the feasibility and future scalability of the digital intervention.

The Patient Health Questionnaire-9 (PHQ-9) and the Generalized Anxiety Disorder-7 (GAD-7) were chosen to measure depressive and anxiety symptoms, respectively, as these emotional states can interfere with the adoption of healthy behaviors and are relevant targets for ACT processes such as acceptance and cognitive defusion. The General Health Questionnaire-12 (GHQ-12) was included to provide a broader measure of general psychological well-being and functioning, complementing the PHQ-9 by assessing non-specific distress; the use of both tools allows for a more nuanced understanding of participants’ mental health status and distinguishes between general distress and specific depressive symptomatology. The Multidimensional Psychological Flexibility Inventory (MPFI) was selected as the primary theoretical outcome, as it directly assesses the six core processes of the ACT Hexaflex model, which the intervention aims to enhance. Two additional instruments, the MEDI-LITE and the International Physical Activity Questionnaire (IPAQ), assess adherence to the Mediterranean diet and physical activity levels, respectively, which are explicit behavioral targets of Demetra’s healthy lifestyle component and relate to the ACT process of committed action. The remaining four tools—User Engagement Scale—Short Form (UES-SF), System Usability Scale (SUS), Chatbot Usability Scale (BUS-11), and the User Mobile Application Rating Scale (uMARS)—were included to measure user engagement, usability, and perceived quality of the digital platform and the virtual coach. These usability and engagement metrics are critical in a feasibility study, as they inform the potential for sustained use and successful integration of ACT-based content into everyday life. This integrated battery of instruments allows for the simultaneous evaluation of psychological, behavioral, and technological engagement outcomes, providing a comprehensive picture of the feasibility and acceptability of the intervention.

An overview of the questionnaires and their administration schedule is provided in Table 2.

The Patient Health Questionnaire-9 (PHQ-9) [26] is used for the diagnosis, monitoring, and determination of depression severity. The PHQ-9 is recommended for both screening and case-finding and can be either self- or hetero-administered. It is an instrument consisting of two questions: the first one concerns the presence of the nine symptoms of depression (according to DSM-IV, also included in DSM-5), especially ‘in the last two weeks’. Through this question, the PHQ-9 score can be determined. Each symptom is assessed on a 4-point scale (0—never, 1—some days, 2—more than half of the days, and 3—almost every day); the second question assesses the functional understanding, caused by the depression, regarding the normal course of the patient’s life. The score of this question does not count towards the total score of the PHQ-9. The test score ranges from 0 to 27: between 5 and 9, depression is considered sub-threshold. A score of 10 is the optimal cut-off for showing clinically relevant depression [27] with three different levels of severity depending on the score [28].

The General Anxiety Disorder-7 (GAD-7) [29], validated in Italian by Pfizer-Italia Srl [25], is a useful self-report instrument for screening generalized anxiety disorder. Starting from the final score, based on cut-offs, it is possible to make a clinical categorization of: no severity, mild severity, moderate severity, or severe severity. It consists of four questions that can be answered using a 4-point scale (0—never, 1—some days, 2—more than half days, and 3—almost every day). Robust, non-parametric statistics were used to verify the one-dimensional nature of the GAD-7 [30].

The General Health Questionnaire (GHQ) [31] is a self-assessment instrument designed to identify mental health disorders and to monitor general psychological well-being. Developed by David Goldberg in 1970, the GHQ is widely used in clinical, research, and public health contexts. The 12 items of the questionnaire are formulated to investigate how the individual was feeling recently, with reference to psychological symptoms (such as anxiety and depression), ability to cope with everyday situations, sleep disturbances, and somatic symptoms. The response is based on a four-point Likert scale, ranging from “much better than usual” to “much worse than usual”, with a maximum score of 36.

The Multidimensional Psychological Flexibility Inventory (MPFI) [32] is an assessment instrument that measures psychological flexibility on several dimensions. It investigates how people adapt their thoughts and behavior in response to changing situations and challenges. The MPFI focuses on various aspects of psychological flexibility, including openness to experiences, present-moment awareness, and value-driven action. The 12 dimensions of flexibility and inflexibility (according to the Hexaflex model) are assessed using 60 Likert scale items ranging from 1 (“never true”) to 6 (“always true”). The Italian version of the scale was developed by Landi in 2021 [33].

A validated questionnaire, MEDI-LITE [34], gives an adherence score to the Mediterranean dietary pattern by assessing consumption of nine food groups. It assigns a numerical score (from 0 to 18), awarding more points for the high-frequency consumption of typical Mediterranean diet foods (e.g., fruit, vegetables, and pulses) and fewer points for the consumption of non-typical foods (e.g., meat and dairy products).

The International Physical Activity Questionnaire (IPAQ) [35,36] is a self-assessment tool that allows for measuring an individual’s level of physical activity. It classifies people into one of three categories (‘inactive’, ‘minimally active’, and ‘HEPA—health-enhancing physical activity—active’) based on the kinds of physical activities they do as part of their everyday lives and the time spent being physically active in the last 7 days. In this study, the short version was used, referring to pre-pregnancy physical activity.

The Chatbot Usability Scale (BUS-11) [37] is a tool designed to assess the usability, effectiveness, and satisfaction of users when interacting with chatbots. This instrument is structured around 11 items covering various aspects of the user experience with chatbots, aiming to provide an in-depth and multidimensional assessment of their usability. The items are answered on a 5-point Likert scale, where 1 equals “strongly disagree” and 5 equals “strongly agree”. The overall score ranges from 11 to 55.

The System Usability Scale (SUS) [38] is a quick and reliable tool for assessing the usability of systems. Developed by Brooke, it consists of 10 items and answers on a Likert scale of 1 to 5. The questionnaire provides an overall score that reflects the usability and applicability of a system or product. The score ranges from 10 to 50, depending on the degree of agreement with phrases such as ‘I found the system very easy to use’.

The User Engagement Scale—Short Form (UES-SF) [39] measures users’ engagement with digital technology through four subscales: focus, aesthetics, perceived interest, and perceived satisfaction. With only 12 items, it provides a quick but effective assessment of user engagement, resulting in scores that can range from 12 to 60 depending on the response given to the Likert scale ranging from 0 to 5, from ‘strongly agree’ to ‘strongly disagree’.

The User Mobile Application Rating Scale (uMARS) [40] is a tool to assess the quality of mobile applications. It consists of 26 items divided into 6 sections on engagement, functionality, aesthetics, information, subjective quality, and perceived impact. This allows for an in-depth and multidimensional assessment of the quality of mobile apps. Each item proposes answers on a Likert scale from 1 to 5, with 1 corresponding to ‘insufficient’ and 5 to ‘excellent’ [41].

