### 2.2. Study Design and Plan

This research project combines the principles of co-design, where stakeholders and final users actively participate in the design process, with a proof-of-concept design phase, to assess the feasibility and initial effectiveness of the designed digital intervention. This type of study requires a small, diverse, and representative sample (overweight pregnant women, healthcare professionals, and researchers) to ensure that the final service is well-designed, user-friendly, and meets the needs of the target audience.

In the psychological component of the intervention, the virtual coach Demetra will engage with participants for a continuous period of six weeks, spanning from the 14th to the 24th week of pregnancy. At the beginning of the program, six self-report questionnaires will be administered, as described in the Collected Parameters section, to establish baseline levels. The intervention will then be delivered through a variety of formats, including text, images, audio, and video. At the conclusion of the program, the same questionnaires will be re-administered to evaluate potential changes in eating habits, psychological well-being, and perceived quality of life.

Additionally, four more questionnaires will be administered to assess usability aspects, specifically user experience (UX) and user engagement (UE). All data collection procedures comply with current Italian regulations concerning personal data protection.

One month after completing the intervention, participants who have provided informed consent will be invited to take part in a semi-structured interview. This qualitative phase aims to explore their experience using Demetra within the TreC Mamma app and to gain insight into their emotional and cognitive responses throughout the process.

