### 2.8. Data Analysis

#### 2.8.1. Quantitative Analysis

Statistical data processing will be conducted using R software, version 4.0.0 [42], IBM SPSS Statistics, version 27.0 [43], Stata 17 [44], and JASP, version 0.18.2 [45].

Categorical variables will be summarized using absolute and percentage frequency distributions, while quantitative variables will be described through appropriate measures of central tendency and variability.

Descriptive analyses will be conducted for both the physical–psychological variables (including depressive and anxiety symptoms, general well-being, experiential avoidance, psychological flexibility, physical activity, and eating habits) and the usability (UX) and user engagement (UE) variables. These analyses will be performed on data collected at the start, during, and at the conclusion of the interaction with Demetra.

The relationships between variables will primarily be examined using specific statistical tests such as the chi-square test, Fisher’s exact test, paired *t*-test, Wilcoxon’s non-parametric tests, and the sign test (depending on whether assumptions are met). This will help identify differences between baseline and post-intervention measurements within the same sample for the variables under study. Additionally, univariate logistic or multinomial regression models will be presented. To control for potential confounding variables, multivariate regression models will be employed, adjusting the effects of explanatory variables on outcome variables accordingly. A *p*-value ≤ 0.05 will be considered statistically significant for all analyses. Furthermore, McNemar’s test and Cochran’s Q test are planned for assessing paired qualitative data [46].

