## Figures and Tables

**Figure 1 ijerph-23-00483-f001:**
[figure not shown]
Overview of the intervention, including timing indications.

**Table 1 ijerph-23-00483-t001:** Summary of the questions of the qualitative interview.

Interaction	How did you find the interaction with the chatbot? Were there enough alternatives among the answers to be given to the chatbot? Which feature of the interaction did you like the most? And the one you liked the least?
Content	Do you feel that the mode of communication (length of sentences, terms used) was appropriate to the content?
Engagement and consistency	Was communicating with the chatbot engaging? In other words, did it encourage you to participate?
General	Do you have any concerns? Do you have any criticisms? Do you think that overall the intervention is suitable for a pregnant woman? from 0 to 10? When do you think would be the ideal time to have this intervention (beginning, middle, or end of pregnancy)?

**Table 2 ijerph-23-00483-t002:** Summary of the questionnaires administered and their timing.

At the Start of the Study (Week 0)	At the End of Week 3	At the End of the Study (Week 6)	Follow-Up (One Month After the End of the Intervention)
PHQ-9		PHQ-9	
GAD-7		GAD-7	
GHQ		GHQ	
MPFI		MPFI	
MEDI-LITE		MEDI-LITE	
IPAQ		IPAQ	
	UES-SF	UES-SF *	
	SUS	SUS *	
	ITA BUS B	ITA BUS B *	
		uMARS *	
			qualitative interview

Note. * These usability questionnaires will be administered the day after those investigating psychological variables, so as not to burden the participant during compilation.

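### The IPAQ is given two incompatible recall windows; with the pre-pregnancy window said to be used in this study, repeating it at week 0 and week 6 does not measure change in current physical activity

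*Protocol article*

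**What the plan says.** **Recall window.** Section 2.6.2 describes the IPAQ as classifying people by their everyday activities and "the time spent being physically active in the last 7 days". The next sentence sets a different period for this study: "In this study, the short version was used, referring to pre-pregnancy physical activity". That sentence is not restricted to one visit.

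**Schedule.** Table 2, captioned "Summary of the questionnaires administered and their timing", lists the IPAQ in the week 0 column and again in the week 6 column.

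**Role.** Section 2.6.2 says the lifestyle instruments are there "to measure adherence to healthy dietary patterns and physical activity levels, which are explicit behavioral targets of the intervention". It then names the MEDI-LITE and the IPAQ as the two that "assess adherence to the Mediterranean diet and physical activity levels, respectively, which are explicit behavioral targets".

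**Analysis.** Section 2.2 says that at the end "the same questionnaires will be re-administered to evaluate potential changes in eating habits, psychological well-being, and perceived quality of life". Section 2.8.1 includes physical activity among the variables to be described ("experiential avoidance, psychological flexibility, physical activity, and eating habits"). It then says of the planned tests: "This will help identify differences between baseline and post-intervention measurements within the same sample for the variables under study". Section 4 adds the aim of observing before-and-after differences in healthy lifestyle behaviors.

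**The concern.** An outcome can show change over six weeks only if its recall window moves with the visit. A window that ended before the first visit stays where it is, so a second administration asks for the same fact again.

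The IPAQ is the only questionnaire in Table 2 that addresses physical activity, and the intervention supplies exercise material organized by trimester (section 2.1). If the pre-pregnancy window is used at both visits, a result of no difference could be reported as no change in activity, and a significant difference could be reported as a change, when neither would bear on what the women were doing. Sections 4 and 5 look ahead to a randomized trial that would build on this study, so a misread activity result could carry over into its design. The week 6 form would also add to a questionnaire load that the Limitations section already regards as a risk to data quality.

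**Working it through.** The article gives no figure for this outcome, so there is none to reproduce. The check compares the recall window with the schedule.

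**Inputs**
- Enrolment is between the 14th and 24th week of gestation (section 2.3), so the pre-pregnancy period is over before week 0 for every participant.
- The psychoeducational program lasts six weeks (section 2.1), with the IPAQ at its start and end (Table 2).
- Two recall windows are stated for the IPAQ (section 2.6.2).

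**Notation, for one participant**
- P: true pre-pregnancy activity
- C0, C6: true current activity at week 0 and week 6
- e0, e6: recall and reporting error at each visit
- D: recorded week 6 value minus recorded week 0 value

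**Reading 1: pre-pregnancy window at both visits (the literal text).**
D = (P + e6) − (P + e0) = e6 − e0.
P cancels, and C0 and C6 never enter. The comparison carries no information on change in current activity, whatever the sample size. The same holds for the three IPAQ categories: the true category is identical at both visits, so any woman who changes category does so through reporting alone.

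**Reading 2: pre-pregnancy window at week 0, last seven days at week 6 (not stated anywhere).**
D = (C6 + e6) − (P + e0) = (C0 − P) + (C6 − C0) + (e6 − e0).
The first term is the shift from before pregnancy to the start of the program, which precedes any exposure to it. It cannot be separated from the second term, which is the one of interest.

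**Reading 3: last seven days at both visits.**
D = (C6 − C0) + (e6 − e0).
This measures change in current activity, but it contradicts the sentence that sets the window for this study.

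Only reading 3 serves the use described in sections 2.6.2, 2.8.1 and 4, and it is the one the study-specific sentence rules out.

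**The case against.** **The wording is ambiguous.** The two windows stand in consecutive sentences and the app's own wording is not shown. A reader might infer that the true change is zero by construction as a settled fact. The documents support that only under reading 1. Reading 1 is the most literal, since nothing limits the pre-pregnancy sentence to week 0, but the conclusion stays conditional on it. The ambiguity does not rescue the plan: reading 2 fails for another reason, and reading 3 requires the text to be corrected.

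**Pre/post use of the IPAQ is partly inferred.** Section 2.8.1 names physical activity in its sentence on descriptive analyses, and the sentence on baseline versus post-intervention differences refers only to the study variables in general. The list of changes in section 2.2, and the list in section 2.6.2 of what the six repeated questionnaires investigate, both leave activity out. These omissions are real. Against them stand the repeat administration in Table 2, the count of six questionnaires at start and end (which needs the IPAQ to reach six), the named role in section 2.6.2 and the aim in section 4. Together they make a before-and-after use the natural reading.

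**The effect on a test cannot be quantified.** A reader might infer that a test on such data would reject at exactly the nominal rate implied by the threshold of p ≤ 0.05. That would need recall error to be distributed alike at both visits. After six weeks of coaching, recollection of earlier activity could drift, and a test on three categories need not attain its nominal level. No rate can be stated from the documents.

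**The study makes no causal claim.** Section 4 concedes that changes may not be due solely to the intervention, and the Limitations section notes the absence of a control group. A reader might infer that the recall window is what prevents an effect of the intervention from being seen. It is not the only obstacle: a correct window would not isolate such an effect in a single-arm study either. The defect is more basic, because current activity at the two visits is not compared at all.

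**Conclusion.** The point holds. The article states two incompatible recall windows for the IPAQ, and the one it assigns to this study does not fit repeated use as a measure of change. On the literal text, the week 6 minus week 0 difference reflects recall or reporting variation only. On the unstated alternative of a pre-pregnancy window at week 0 alone, the comparison mixes the effect of pregnancy with any change during the program.

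This rests on two assumptions: that the questionnaire in the app follows the study-specific sentence, and that the IPAQ is meant as a before-and-after outcome, which several sections support but none states in a single explicit sentence.

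The loss is complete for this outcome but confined to it. The primary objective is co-design together with exploration of user experience and engagement (section 1.3.1), pre/post well-being is secondary (section 1.3.2), and the sample-size rationale in section 2.4 does not mention the IPAQ. It should be fixed, but it does not threaten the study's main purpose. It is more than missing detail: an analysis plan cannot recover current activity that was never asked about.

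**What to change.** Use the IPAQ short form with the last-seven-days window at both week 0 and week 6, and base the pre/post comparison on that version. If pre-pregnancy activity is wanted, ask it once at enrolment, label it separately in Table 2, and use it only as a descriptor or covariate. Correct the sentence in section 2.6.2 so that one window is stated for each administration, and name physical activity consistently in sections 2.2, 2.6.2 and 2.8.1.

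If the sponsor prefers to keep only the pre-pregnancy version, the alternative is to drop the week 6 administration, remove the IPAQ from the pre/post analysis, and accept that the study has no questionnaire measure of change in activity.

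The cost is a wording change in the app and a few sentences in the protocol. If both versions are kept, there is one short extra form at week 0, a modest addition to a battery whose length is already acknowledged as a burden. The change restores measurement of change in current activity. It does not allow that change to be attributed to the intervention, and the report should say so.
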